## Abstract

**Introduction::**

Genetic alterations of *KIT* gene are known to be one of the major causes of melanoma. Those are more common in the mucous and acral subtypes and KIT is regarded as major oncogene in Asian melanomas, where the prevalence of these subtypes is high. Up to date, several clinical trials have been conducted to target *KIT* gene alterations in melanoma with unsatisfied efficacies. Imatinib mesylate, a small-molecule inhibitor of the KIT tyrosine kinase, provides a rapid but not durable clinical response in *KIT*-mutant melanoma. Meanwhile, recent basic and clinical evidence have revealed another aspect of KIT-targeted therapy, namely the enhancement of antitumor activity of immune checkpoint inhibitors. Herein, we designed clinical trial of co-administrating imatinib mesylate and pembrolizumab (anti-PD-1 antibody) to evaluate its safety and efficacy.

**Methods and analysis::**

This is an open-label, single-arm, phase I/II clinical trial involving Japanese patients with metastatic *KIT*-mutant melanoma that are refractory to standard therapy including anti-PD-1 therapy. Phase I study is a dose-escalation study comprising two dose levels of imatinib mesylate (200 and 400 mg/day, respectively) with fixed dose of pembrolizumab (200 mg every 3 weeks) to evaluate safety and tolerability and determine recommended phase II dose. The primary endpoint of the phase II study is the objective response rate after 4 cycles (3 weeks/cycle) of pembrolizumab and imatinib mesylate at the dose determined in phase I, based on RECIST version 1.1. A Simon's minimax two-stage design is employed to test the null hypothesis of a 5% response rate vs 30% alternative, which will be rejected when a lower confidence limit of two-sided 90% confidence interval of true response rate is over than threshold response rate. The secondary endpoints include progression free survival, overall survival, best overall response and incidence of adverse events. Totally, a target size of 22 patients will be expected.

**Discussion::**

If this study shows efficacy and acceptable safety profile, it will contribute to the development of novel treatment option for patients with *KIT*-mutant melanoma that are refractory to standard therapy.

**Trial registration::**

NCT04546074. Date of Registration: September 11, 2020 (https://clinicaltrials.gov/ct2/show/NCT04546074). Date of First Participant Enrollment: December 23, 2020.

## Introduction

1

KIT is a type III transmembrane receptor. Upon the biding with its ligand, it triggers activation of downstream signalling pathways to promote cell growth, survival, and migration. Gain-of-function mutations of *KIT* gene have been found in several cancers, hence it is recognized as an oncogene. Prevalence of the alteration of *KIT* gene in melanoma is associated with clinical subtypes, which is more common in acral and mucosal subtypes.^[1]^ Gene amplification is found in about 26% of mucosal and 27% of acral types, and mutation is found in about 25% of mucosal and 21% of acral types.^[2]^ As acral and mucosal type melanomas account for the majority in Asian melanoma, *KIT* gene is regarded as major oncogene causing melanoma in Asia.^[2–4]^

KIT-targeted therapies have not shown satisfactory effect in melanoma to date. While several KIT tyrosine kinase inhibitors (KITi) have shown certain tumor shrinkage effect on *KIT*-mutant melanoma as a monotherapy (ORR; 16–29%), those effects were non-durable (median PFS; 2.8–3.7 months).^[5–11]^ Meanwhile, several preclinical data have shown the other role of KITi that they do not only target tumoral *KIT* gene products but also modulates key signalling pathways of immune cells that are involved in cancer immunosurveillance.^[12]^ In addition, KITi may promote antitumor immunity and exhaust synergistic anti-tumor effect in combination with immune checkpoint inhibitors (ICIs).^[13,14]^ Furthermore, a melanoma patient with *KIT* mutation who was refractory to anti-PD-1 monotherapy has been successfully treated with a combined administration of imatinib mesylate and anti-PD-1 antibody.^[15,16]^

Based on these promising evidences of ICI and KITi combination, we proposed to conduct the phase I/II clinical trial of imatinib mesylate (KITi) with pembrolizumab (anti-PD-1 antibody) for *KIT*-mutant melanoma patients who progressed after ICIs.

## Methods/design

2

### Objectives and study setting

2.1

This study is a single-arm, open-label, phase I/II clinical trial aiming to evaluate the safety, tolerability, and response rate data of imatinib mesylate and pembrolizumab in patients with refractory *KIT* mutant malignant melanoma. The recruitment of study participants started in September 2020 and will continue until a total of 22 participants are registered.

### Study design

2.2

The phase I study is a dose-escalation study comprising two dose levels of imatinib mesylate (200 and 400 mg/day, respectively) with fixed dose of pembrolizumab (200 mg every 3 weeks) to evaluate safety and tolerability and identify maximum tolerated dose/administered, and determine recommended phase II dose (RD).

In phase II study, a Simon's minimax two-stage design is employed to test the null hypothesis of a 5% RR vs 30% alternative (1-sided α 0.05, power 80%, ≥1/7 RR to continue to total of 3 ≥ 14). The treatment period with the combination therapy of both studies will continue every 21 days for up to 33 cycles (∼2 years) as long as patients are receiving benefit from treatment and have not had disease progression or met any criteria for study withdrawal.

The trial design is depicted in Figure 1.

**Figure 1 F1:**
[figure not shown]
Flow chart of phase I study.

### Inclusion criteria

2.3

1.Age 20 years or older on day of signing consent.2.Histologically confirmed melanoma.3.Unresectable or metastatic melanoma with *KIT* mutations detected by next-generation sequencing which was performed at clinical laboratories accredited by international standards such as Clinical Laboratory Improvement Amendments (CLIA) and College of American Pathologists (CAP) certification.4.Progression on treatment with an anti-PD-1/L1 Ab administered either as monotherapy, or in combination with other checkpoint inhibitors or other therapies. PD-1 treatment progression is defined by meeting all the following criteria:a.The patient received at least 2 doses of an approved anti-PD-1/L1 Ab.b.The patient has demonstrated disease progression after PD-1/L1 Ab as defined by RECIST 1.1.The initial evidence of disease progression is to be confirmed by second assessment no less than 4 weeks from the date of the first documented progressive disease, in the absence of rapid clinical progression. This determination is made by the investigator. Once progressive disease is confirmed, the initial date of progressive disease documentation will be considered the date of disease progression.c.Progressive disease has been documented within 12 weeks from the last dose of anti-PD-1/L1 Ab or during the treatment. In adjuvant therapy, progressive disease has been documented within 6 months from the last dose of anti-PD-1/L1 Ab or during the treatment.5.No prior treatment with KIT inhibitors.6.Completed previous therapies 21 days prior to enrollment on study.7.The presence of at least one measurable lesion by CT or MRI per RECIST 1.1 criteria as determined by the local site investigator/radiology assessment within 14 days prior to enrollment on study.8.An Eastern Cooperative Oncology Group (ECOG) performance status 0 to 1.9.Life expectancy of >90 days10.No active central nervous system (CNS) metastases. Patients with previously treated brain metastases may participate provided they are stable (without evidence of progression by imaging for at least 28 days before enrollment on study and any neurologic symptoms).11.If female of childbearing potential, must be willing to use an adequate method of contraception and agree not to breastfeed for the course of the study through 120 days after the last dose of study medication. If male of childbearing potential, must agree to use an adequate method of contraception for the course of the study through 120 days after the last dose of study medication.12.Laboratory parameters within Protocol-defined range. The screening laboratory tests below must be ≤14 days before enrollment on study.a.White blood cell count ≥2000/mm^3^ and absolute neutrophil count ≥1500/mm^3^.b.Platelets ≥ 100,000/mm^3^.c.Hemoglobin ≥ 9 g/dL.d.Aspartate aminotransferase (AST), alanine aminotransferase (ALT) ≤ 150 IU/L.e.Bilirubin ≤ 2.0 mg/dL.f.Serum creatinine ≤ 1.5 mg/dL.13.Be willing and able to review, understand and provide written consent before starting therapy.

### Exclusion criteria

2.4

1.Seropositive for hepatitis B antigen, or hepatitis C antibody.Even if negative for HBs antigen, patients who are positive for HBs antibody or HBc antibody and amount of HBV-DNA exceed detection sensitivity are excluded from the study.2.History of human immunodeficiency virus (HIV) (HIV 1/2 antibodies).3.History of (no-infectious) pneumonitis that required steroids or present pneumonitis.4.Ongoing or active infections, symptomatic heart failure, unstable angina pectoris, cardiac arrhythmias, interstitial pneumonia, pneumonitis, or psychiatric disorders that would interfere with cooperation with the requirements of the study.5.Superior vena cava syndrome, pericardial effusion, pleural effusion, or ascites of grade 3 or higher.6.Gastrointestinal condition that may affect drug absorption.7.Receiving or necessary to continue administering CYP3A4 inhibitors or drugs metabolized by CYP3A4.8.Additional malignancy that is progressing or requires active treatment. Exceptions include cancers that have not recurred for at least 3 years before enrollment on study and early stage cancers (carcinoma in situ or stage 1) treated with curative intent, basal cell carcinoma of the skin, or superficial bladder cancer that has undergone potentially curative therapy.9.Active autoimmune disease that has required systemic treatment in past 2 years.10.History of organ transplantation including hematopoietic stem cell transplantation.11.Receiving chronic systemic steroid therapy. Replacement therapy (e.g., thyroxine, insulin, or physiologic corticosteroid replacement therapy for adrenal or pituitary insufficiency, etc) is not considered a form of systemic treatment.12.Pregnant women and breastfeeding woman.13.Having received live vaccine within 30 days before the first dose of study treatment. Examples of live vaccines include, but are not limited to, the following: measles, mumps, rubella, chicken pox, yellow fever, rabies, Bacillus Calmette-Guerin (BCG), and typhoid vaccine. Seasonal influenza vaccines for injection are generally killed virus vaccines and are allowed; however, intranasal influenza vaccines (e.g., FluMist) are live attenuated vaccines and are not allowed.14.History or current evidence of any condition, therapy, or laboratory abnormality that might confound the results of the study, interfere with the patient's participation for the full duration of the study, or is not in the best interest of the patient to participate, in the opinion of the treating investigator.

### Ethics approval and consent to participate

2.5

This study is being conducted in accordance with the principles expressed in the Declaration of Helsinki, Japanese Clinical Research Act and SPIRIT (Standard Protocol Items: Recommendations for Interventional Trials) guidelines, and conducted as “Advanced medicine” authorized by the Ministry of Health, Labor, and Welfare (MHLW). The protocol version 1.3 was approved by Keio Certified Review Board (CRB3180017) in November 2019 and MHLW.

### Endpoints

2.6

The primary outcome of phase I study is the dose limiting toxicities (DLT) rates of pembrolizumab and imatinib mesylate combination therapy. The primary outcome of phase II study is the objective response rate (ORR) of treatment with recommended dose of imatinib mesylate with fixed dose of pembrolizumab in 12 weeks according to Response Evaluation Criteria in Solid Tumors (RECIST) version 1.1. The patient of the efficacy evaluation includes those who received treatment with RD in the phase I study. Secondary outcome measures include progression-free survival (PFS), overall survival (OS), best overall response (BOR), and incidence of adverse events (AEs) graded using the National Cancer Institute (NCI) Common Terminology Criteria for Adverse Events (CTCAE) version 5.0. PFS is defined as the time from date of registration until the earliest date of disease progression or death from any cause, whichever comes first. OS is defined as the time from date of registration to date of death due to any cause. BOR is defined from the overall efficacy determined by the end of this trial according to RECIST 1.1. Determining CR and PR requires radiologic confirmation by continuous evaluation over an interval of 4 weeks.

### Treatment in phase I study

2.7

Phase I study is 3+3 dose-escalation study comprising two dose levels of imatinib mesylate with fixed dose of pembrolizumab. This study will be broken into 2 levels of 3 to 6 patients each level. The cycle length of regimen is 21 days. Each patient will receive 2 cycles of imatinib mesylate and pembrolizumab combination therapy and assessed for DLT at day 42 (±2). The first level (Level 1) of patients will receive the lowest dosing regimen, oral imatinib mesylate 200 mg quaque die (QD) for 21days and intravenous pembrolizumab 200 mg on day1 every 21 days, with subsequent cohorts receiving increasing doses of imatinib mesylate, 400 mg QD. After the RD has been determined, this dosage scheme will be used to treat patients in phase II study. If patients in phase I show no DLTs followed by non-progressive disease, they will continue with combination therapy for up to 2 years.

Escalation scheme is as follows (Fig. 1):

1.If DLT is not observed in all 3 cases in Level 1, proceed to enrollment of Level 2.2.If DLT is observed in one of 3 cases in Level 1, add further 3 cases, anda.If DLT is observed in 1 of total 6 cases, proceed to enrollment of Level 2.b.If DLT is observed 2 or more of 6 cases, the study is discontinued.3.If DLT is observed 2 of 3 cases in Level 1, the study is discontinued.Regarding the transition to Level 2, the evaluation of the investigator will be discussed and judged by Efficacy and Safety Evaluation Committee.4.If DLT is not observed in all 3 cases in Level 2, dose of Level 2 is determined as RD.5.If DLT is observed in one of 3 cases in Level 2 cohort, add further 3 cases, anda.If DLT is observed in 1 of total 6 cases, dose of Level 2 is determined as RD.b.If DLT is observed 2 or more of 6 cases, dose of Level 1 is determined as RD.6.If DLT is observed 2 of 3 cases in Level 2, dose of Level 1 is determined as RD.The evaluation of the RD by the investigator will be discussed and judged by Efficacy and Safety Evaluation Committee.

### Definition of DLT

2.8

DLT will be assessed by physical examination, observing and questioning patients regarding adverse experiences, and monitoring clinical chemistry and hematology by the treating investigator. DLT is defined as any:

Any of the Grade 3 non-hematologic toxicity as defined in CTCAE v5.0 excluding the follows:∘Fatigue, infusion reaction and alopecia,∘Nausea, vomiting, diarrhea and electrolyte imbalances responsive to appropriate medications <7 daysAny of the Grade 4 hematologic adverse events for ≥5 days excluding febrile neutropeniaFebrile neutropeniaRequiring discontinuing imatinib mesylate for at least 8 days due to an adverse eventAny severe or life-threatening complication or abnormality not defined in the CTCAE v5.0 that is attributable to the therapy

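### The DLT definition names only Grade 3 for non-haematological toxicity, so CTCAE-defined Grade 4 and 5 events count only if imatinib is stopped for at least 8 days

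*Protocol article*

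**What the plan says.** Section 2.8 (Definition of DLT) lists five alternative criteria:

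1. Non-haematological: "Any of the Grade 3 non-hematologic toxicity as defined in CTCAE v5.0 excluding the follows". The exclusions are fatigue, infusion reaction and alopecia, and also nausea, vomiting, diarrhoea and electrolyte disturbance that respond to medication in under 7 days.
2. Haematological: Grade 4 lasting 5 days or more.
3. Febrile neutropenia.
4. An adverse event that requires imatinib to be stopped for at least 8 days.
5. A "severe or life-threatening complication or abnormality not defined in the CTCAE v5.0 that is attributable to the therapy".

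Section 2.6 (Endpoints) gives the count its role: "The primary outcome of phase I study is the dose limiting toxicities (DLT) rates of pembrolizumab and imatinib mesylate combination therapy".

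Section 2.7 (Treatment in phase I study) turns the count into decisions. At Level 1, "If DLT is observed in one of 3 cases in Level 1, add further 3 cases"; one DLT in six then allows escalation, and two or more stop the study. At Level 2, "If DLT is observed 2 or more of 6 cases, dose of Level 1 is determined as RD". The same section adds a review step: "The evaluation of the RD by the investigator will be discussed and judged by Efficacy and Safety Evaluation Committee". The move to Level 2 is reviewed in the same way.

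**The concern.** A DLT definition should be monotone in severity: if a Grade 3 event counts, a worse event of the same kind must count too. The printed list does not guarantee this. Grade 4 appears only for haematological events, Grade 5 does not appear, and the clause that might have served as a safety net is closed to anything CTCAE defines.

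The remaining route, criterion 4, depends on imatinib alone, although the endpoint is the DLT rate of the combination. An event handled by holding pembrolizumab, with imatinib continued or restarted within 8 days, falls outside it.

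In a 3+3 design with at most six patients per level, one uncounted event can change the outcome. At stake are the reported phase I primary endpoint, the decision to escalate from 200 to 400 mg/day, and the dose carried into phase II.

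**Working it through.** **Step 1: test one event against the list.** Take a non-haematological event that CTCAE v5.0 defines and that is graded 4.

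| Criterion in 2.8 | Met? |
|---|---|
| 1. Grade 3 non-haematological | No: only Grade 3 is named |
| 2. Grade 4 for 5 days or more | No: haematological only |
| 3. Febrile neutropenia | No |
| 4. Imatinib stopped for at least 8 days | Only if that happens |
| 5. Severe or life-threatening, outside CTCAE | No: CTCAE defines the event |

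Grade 5 gives the same result. For a rapid death it is also unclear whether criterion 4 is met. No other section says that Grade 3 includes higher grades or that a treatment-related death is a DLT. Where the article means a threshold it can say so: exclusion criterion 5 (section 2.4) has "pleural effusion, or ascites of grade 3 or higher".

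**Step 2: effect of one uncounted event under 2.7.**

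- *Two of six read as one of six.* The decision changes directly. At Level 1, discontinuation becomes escalation; at Level 2, a recommended dose of 200 mg becomes 400 mg.
- *One of three read as none of three.* The three-patient expansion is skipped. The final decision differs only if at least one of those three would have had a DLT, with probability 1 − (1 − p)³. At assumed true DLT rates p of 10%, 20% and 30%:
  - 1 − 0.9³ = 0.271
  - 1 − 0.8³ = 0.488
  - 1 − 0.7³ = 0.657

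**Step 3: chance that a level passes.** A level passes with 0/3, or with 1/3 followed by 0/3. Three DLTs in three patients, which 2.7 does not list, is treated as two in three. With counted DLT rate p:

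P(p) = (1 − p)³ + 3p(1 − p)² × (1 − p)³

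For example, P(0.30) = 0.343 + 0.9 × 0.16807 = 0.494, and P(0.20) = 0.512 + 0.6 × 0.32768 = 0.709.

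Let g be the part of the true rate that is Grade 4-5 non-haematological, and c the share of those events that the 8-day criterion catches. The counted rate is then the true rate − g(1 − c). The documents give none of these figures; all are assumptions.

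| True rate | g | c = 0 | c = 0.5 | c = 0.8 | c = 1 |
|---|---|---|---|---|---|
| 30% | 10 points | 70.9% | 60.0% | 53.6% | 49.4% |
| 30% | 5 points | 60.0% | 54.6% | 51.5% | 49.4% |
| 20% | 10 points | 90.6% | 81.4% | 75.2% | 70.9% |

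At a true rate of 30%, the excess chance of passing a level runs from 0 to 70.9 − 49.4 = 21.5 percentage points. At 80% capture it is 53.6 − 49.4 = 4.2 points for g = 10, and 51.5 − 49.4 = 2.1 points for g = 5.

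**The case against.** The strongest reply is that the meaning is obvious. No investigator would count a Grade 3 event and ignore a Grade 4 event of the same kind, and the calculation above itself reads 2.7 sensibly when it treats three DLTs in three as two in three. That the intent was Grade 3 or higher is very probable. It is a reason to correct the text, and adding those words alone would not finish the job: the listed exclusions carry no grade limit, so a Grade 4 infusion reaction would still be exempt by grade.

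A symbol may have been lost. One such sign survives in 2.8 (5 days or more), but another is misplaced in section 2.2, where the phase II rule is given. A lost sign therefore seems unlikely but cannot be ruled out.

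Other provisions narrow the gap. Criterion 4 has no grade or organ limit and does not ask which drug caused the event. Section 2.10 takes a patient off the trial for severe adverse events that the investigator finds unacceptable; if that ends imatinib, criterion 4 is met. A fatal toxicity also ends imatinib, so death may well be covered. These points stand. What is left is mainly a Grade 4 event, within the 42-day assessment period, after which imatinib continues or restarts within 8 days.

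The Efficacy and Safety Evaluation Committee judges both escalation and the recommended dose. That lowers the practical risk, but it does not change which events the definition counts or the DLT rate reported.

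Finally, this is a journal article, and the operative protocol (version 1.3) is not shown. But the article prints a full list with grades, durations and exclusions, so this is a stated rule rather than a detail left out.

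**Conclusion.** The concern holds for the wording as printed and should be fixed. CTCAE-defined Grade 4 and 5 non-haematological events are not DLTs by grade, and only the 8-day imatinib criterion can bring them in. Confidence in that reading is high. Whether DLTs will in fact be miscounted is less certain: it depends on the wording of version 1.3, on how investigators read the rule, and on how often such events leave imatinib running.

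Under the assumed true DLT rate of 30%, the chance of wrongly passing a level grows by 0 to about 21 percentage points. The upper end requires a third of DLTs to be Grade 4-5 non-haematological and none to be caught by the 8-day criterion; a few points is more plausible if that criterion catches most of them. The model also assumes that a patient with an uncounted event has no other qualifying DLT.

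**What to change.** In section 2.8:

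- Change the first criterion to Grade 3 or higher non-haematological toxicity as defined in CTCAE v5.0.
- Limit the listed exclusions to Grade 3, so that a Grade 4 infusion reaction or Grade 4 diarrhoea, for example, is a DLT.
- Add any death not clearly due to disease progression as a DLT.

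Then check version 1.3. If it already has the broader threshold, only the article needs correcting. If it has the same wording, amend it and re-read the phase I events already recorded against the corrected definition. That is at most 12 patients (two levels of up to 6).

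The cost is one or two lines of text. Sample size, alpha and power do not change.

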### Treatment in phase II study

2.9

A sample size of 7 in each stage of the 2-stage design is required to detect efficacy. Eligible patients receive the dose determined in phase I cohort. The subject of the efficacy evaluation includes those who received treatment with RD in the phase I study. The cycle length of regimen is 21 days. Each patient will receive 4 cycles of imatinib mesylate and pembrolizumab combination therapy and assessed for clinical efficacy at week 12 (±7 days) at the site per RECIST 1.1. After evaluating 7 patients for response in 4 cycles of the first stage, the trial would be terminated if no patient had a CR, PR. If at least one patient met these criteria, an additional 7 patients would be enrolled for the second stage. A total of 14 (16 at maximum) patients including those who received treatment with RD in the phase I study will be assessed. At the end of the trial, if the total number of responses (CR + PR) is 3 or more, the combination would be considered promising. Each patient who shows non-PD, they are allowed to continue with combination therapy for up to 2 years. Patients will be assessed for response criteria every 4 cycles.

